
#### Relatives—relevant outcomes and measurements

Relevant outcomes and measurements for relatives include the following:
The mental disorder, the disorder severity and the restrictions in daily life of the participants’ mentally ill relatives will be assessed with a separate questionnaire.Changes in the relatives’ knowledge, attitudes and experiences regarding available treatments (*see* objective 2) will be evaluated using the same developed checklist that was used for patients.Satisfaction with treatment (*see* objective 4) from the perspective of the relatives will be assessed with the ZUF-8 (*see* above).Changes in treatment needs and coverage of needs of the mentally ill relatives (see objective 5) will be assessed by using the CAN-EU (*see* above).Quality of Life (QoL) of relatives of patients with severe mental illness (see objective 6) will be measured with the WHOQOL-BREF (*see* above).Relatives’ burden of care (*see* objective 8) will be assessed using the ‘Burden Assessment scale’ (BAS) [25]. The BAS is a 19-item scale that focuses on specific subjective and objective consequences of relatives caring for persons with severe mental disorders within the past 6 months. Answers are given on a 4-point Likert scale ranging from (1) not at all to (4) very much, with higher values indicating stronger burden.Sociodemographic data of the relatives will be assessed with a separate questionnaire.

### Data collection and management

Patients and relatives will be interviewed by the study staff at three time points: shortly after admission (baseline, t_0_), 2 weeks after visiting both parts of the group sessions (intervention group) or 6 weeks after t_0_ (control group) (t_1_), and 6 months after t_0_ (t_2,_ both groups) (*see* Table 1). Due to the large number of outcomes to be measured, the interview can, if necessary, be divided into several appointments in order to avoid excessive demands on the participants. The collected data will be recorded on paper and subsequently entered in a standardized data form at the recruiting centres. Data entry will be done by one study member and checked by another member (double check) to avoid mistakes. Data will be stored in a secured computerised database centrally at the study centre Günzburg. Participant files will be maintained in storage for a period of 10 years after completion of the study.

**Table 1 Tab1:**
[figure not shown]
Template for the schedule of enrolment, interventions and assessments

To avoid follow-up losses, study staff will contact the participants regularly, for example by visiting the subjects during their inpatient stay. After discharge, they will be informed by newsletter and will be informed by phone or (e)-mail about upcoming data collection. Furthermore, the participants will be offered interview appointments after discharge that can be carried out at the participant’s home or by telephone.

Participants may withdraw from the study for any reason at any time. Participants who do not follow the intervention schedule will be interviewed as scheduled during the follow-up appointments. If possible, reasons for dropout are recorded.

### Data monitoring

A data monitoring committee was not established because no risks are to be expected for the participants in the intervention or the control group.

### Quality control

Prior to the start of the study, the study staff in all recruiting clinics will receive comprehensive assessment training. This rigorous training and regular meetings during the recruitment phase will ensure adherence to the protocol by all researchers involved in the study. During all study phases, the study lead will supervise the study.

### Sample size

Sample size calculation was based on a two-step procedure due to the hierarchical data structure. In the first step, the sample size for an individual randomized study is calculated. Based on studies using the ‘empowerment in the process of psychiatric treatment of patients with affective and schizophrenia disorders (EPAS)’ scale [26], a medium effect (0.4 SD units) of the implementation intervention on the primary endpoint is expected. This effect is detectable with an error probability of 5% (alpha) and a power of 80% by a t-test for independent samples with a sample size of 2 × 100 participants (200 in total).

The second step takes the cluster structure of the data into account. We assume that each centre recruits 35 patients (m) on average. The design effect (DE) is needed for the inflation of the group sample size: DE = 1 + (m - 1) * ICC with the fixed cluster size m and the intra-cluster correlation coefficient ICC. We assume a liberal intra-class correlation coefficient of 0.02 to control for the correlation of the outcome of participants of the same centre. Thereby, the DE is 1 + (35–1) * 0.02 = 1.68, which gives a sample size of 200 × 1.68 = 336 patients. As every centre recruits 35 patients on average, 10 centres are needed for the trial. Due to the severity of the disease in the patient population, case number planning assumes that 70% of patients can be reached 6 months after t_0_, so that an oversampling to (35/0.7) 50 patients per study centre will be recruited, resulting in 10 centres * 50 patients = 500 participants (2 × 250) as the overall sample size. This 70% estimate is based on experiences at the Günzburg site from three studies conducted with similar populations [27–29].

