### Randomisation

The randomisation of the centres (cluster) to the intervention or control group will be done externally by the Institute for Epidemiology and Medical Biometry, Ulm University, Ulm, Germany, by a stratified block randomisation. The 10 recruiting centres will be randomised 1:1 to the intervention and control group using the size of centre (small, large) as strata. The random assignment will be performed by the randomisation program ROM [9].

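### The 80% power is carried from an individual-level t-test into a comparison of 5 with 5 centres without allowing for 7–8 degrees of freedom; on the calculation's own inputs, before baseline adjustment, it is about 70%

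*Protocol article*

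**What the plan says.** The protocol article's Sample size section works in two steps.

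- **Step 1, individual randomisation.** The planning effect is "a medium effect (0.4 SD units) of the implementation intervention on the primary endpoint is expected". The section then states: "This effect is detectable with an error probability of 5% (alpha) and a power of 80% by a t-test for independent samples", with 100 patients per arm.
- **Step 2, clustering.** The section assumes 35 patients per centre ("We assume that each centre recruits 35 patients (m) on average") and an ICC of 0.02 ("We assume a liberal intra-class correlation coefficient of 0.02"). It defines the design effect "with the fixed cluster size m and the intra-cluster correlation coefficient ICC", obtains 1.68 and 336 patients, and concludes: "As every centre recruits 35 patients on average, 10 centres are needed for the trial". Division by 0.7 for loss to follow-up gives 50 per centre and 500 in total, 250 per arm.

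The Randomisation section allocates the 10 centres 1:1, "using the size of centre (small, large) as strata". The Statistical methods section specifies a hierarchical linear model for EPAS at 6 months, with intervention, baseline EPAS, centre and centre size, tested at 5%.

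No step of the sizing uses a between-centre t distribution, adds a centre for small-sample reasons, or takes credit for the baseline covariate.

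**The concern.** Every patient in a centre receives the same condition, so the intervention effect is estimated from differences between centres. With 10 centres there is little information about the between-centre variance, and the test needs a much larger critical value than a t-test on 198 degrees of freedom. Multiplying by a design effect does not supply this. It is a good approximation with many clusters and a poor one with ten.

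The 80% is the only power the article gives for its single confirmatory test. If its basis is too favourable, a null result would be read as coming from a trial with a 20% chance of missing 0.4 SD, when on the calculation's own terms that chance is nearer 30%.

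**Working it through.** **Inputs.** Effect 0.4 SD; alpha 5% (taken as two-sided, which reproduces the plan's figure); ICC 0.02; 35 analysed per centre; 10 centres (all from Sample size). The 5 v 5 split is inferred from 10 centres, 1:1 allocation and 2 × 250 patients. Centre is read as the random cluster effect of the hierarchical model.

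**1. The plan's own figures reproduce.**
- Two-sample t-test, 100 per arm, 198 df: power 80.4%.
- DE = 1 + (35 − 1) × 0.02 = 1.68; 200 × 1.68 = 336; 336/35 = 9.6, rounded up to 10 centres.
- 35/0.7 = 50 per centre; 10 × 50 = 500.

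**2. The same inputs with between-centre degrees of freedom.**
- df = 2 × 5 − 2 = 8, or 7 with centre size as a centre-level covariate.
- Two-sided 5% critical values: 1.97 (198 df), 2.31 (8 df), 2.36 (7 df).
- SE = √(2 × DE / n per arm); noncentrality = 0.4/SE; power from the noncentral t.

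| Analysed | SE | Noncentrality | 8 df | 7 df |
|---|---|---|---|---|
| 350 (5 × 35 per arm) | √(2 × 1.68/175) = 0.139 | 2.887 | 71.6% | 69.8% |
| 336 (DE 1.68) | √(2 × 1.68/168) = 0.141 | 2.828 | 69.8% | 68.1% |

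With a large-sample reference, 350 analysed patients would give 82%. The loss therefore comes from the degrees of freedom, not the variance. Using 1.96 in the analysis would keep the nominal power only by raising the type I error to about 8.6% (8 df) or 9.1% (7 df), against the 5% the article fixes.

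**3. Detectable effect.** With 350 analysed, 80% power is reached at 0.444 SD (8 df) or 0.453 SD (7 df).

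**4. Sensitivity to the ICC** (350 analysed, no covariate gain):

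| ICC | DE | 8 df | 7 df |
|---|---|---|---|
| 0.01 | 1.34 | 80.7% | 79.1% |
| 0.02 | 1.68 | 71.6% | 69.8% |
| 0.03 | 2.02 | 63.7% | 62.0% |
| 0.05 | 2.70 | 51.7% | 50.1% |

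**5. What baseline adjustment would have to do.** For 80% power at 0.4 SD the variance must fall by the factor (0.4/0.4435)² = 0.813 on 8 df, or (0.4/0.4531)² = 0.779 on 7 df. Let ρ be the baseline to 6-month correlation, and assume that adjustment shrinks both variance components equally.
- *0.4 in SD units of EPAS at 6 months:* the factor is 1 − ρ². This needs ρ ≥ √(1 − 0.813) = 0.43 (8 df) or √(1 − 0.779) = 0.47 (7 df).
- *0.4 in SD units of the change score:* change variance 2σ²(1 − ρ) is set to 1 and the adjusted variance is σ²(1 − ρ²), so the factor is (1 + ρ)/2. This needs ρ ≤ 2 × 0.813 − 1 = 0.63 (8 df) or 2 × 0.779 − 1 = 0.56 (7 df).
- At ρ = 0.5 both factors equal 0.75, and power is 83.0% (8 df) or 81.5% (7 df).
- If only patient-level variance shrinks, the raw-unit threshold rises to about 0.57 (8 df) or 0.61 (7 df).

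**The case against.** The strongest reply is that about 70% describes an unadjusted comparison which the trial will not run. The confirmatory model includes baseline EPAS. It is one-sided to charge a degree of freedom for centre size, which is in that model, and give no credit for the baseline covariate in the same model. This stands. A reader might infer that the trial as designed has only 70% power, and the document does not support that.

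Nor can it be said that 80% is recovered only above some correlation. The Primary outcome section describes the endpoint as a change, so the 0.4 may be in change-score units, and the condition then becomes an upper limit on the correlation. The article settles neither the unit nor the correlation.

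Other parts of the reply also stand:
- The arithmetic is correct at every step, and the 80% sentence is true of the individual-level test it describes. The fault is one of method: that figure is carried to the cluster design unchanged.
- The ICC cuts both ways. At 0.01, power is 79–81% without any covariate gain.
- Retention above the planned 70% would help: 40 analysed per centre gives 74.8%/73.0% (8/7 df) and 45 gives 77.3%/75.6%. Neither reaches 80%, and the sizing itself assumes 35.
- Small and large strata might be read as showing unequal cluster sizes, which would cost further power. They do not show it, because the target is 50 patients in every centre.

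The argument that degrees of freedom belong in the analysis plan does not rescue the figure. The method for the analysis may well be set there, but the power is stated here, and at the stated inputs a test that holds 5% has about 70% power before adjustment.

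**Conclusion.** The stated 80% does not follow from the calculation given for it. With 5 v 5 centres of 35 analysed patients, ICC 0.02, 0.4 SD and no covariate gain, power is 71.6% on 8 df or 69.8% on 7 df, some 8 to 10 points short of 80%. This rests on between-centre degrees of freedom, equal cluster sizes and a two-sided 5% test.

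Whether the planned baseline-adjusted analysis reaches 80% is open. It may well do so, but that depends on a correlation and an SD unit that the article does not state and that the sizing does not use. The shortfall is established for the sample-size calculation, not for the trial's eventual analysis. The size of the type I error is not in question unless the analysis uses large-sample critical values, which the article does not say it will.

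**What to change.** Keep 10 centres, 500 patients, the model and the 5% level. Then do one of two things in the Sample size section:

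1. Restate the power as about 70% for 0.4 SD before baseline adjustment (80% for about 0.45 SD), on 7–8 between-centre degrees of freedom with ICC 0.02; or
2. Re-derive it for the planned baseline-adjusted model with 7 df, stating the assumed baseline to 6-month correlation, its source, and whether 0.4 SD is in raw 6-month or change-score units.

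In either case show the range over ICC 0.01 to 0.05, which before adjustment runs from 79–81% down to 50–52%.

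The cost is a rewrite of one section and a less favourable, or more openly conditional, power figure. No patients or centres are added.

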### Randomisation

The randomisation of the centres (cluster) to the intervention or control group will be done externally by the Institute for Epidemiology and Medical Biometry, Ulm University, Ulm, Germany, by a stratified block randomisation. The 10 recruiting centres will be randomised 1:1 to the intervention and control group using the size of centre (small, large) as strata. The random assignment will be performed by the randomisation program ROM [9].

### Statistical methods

First, the sociodemographic and clinical characteristics will be listed. Categorical variables will be described as absolute and relative frequencies and with graphical representation (e.g., bar chart). Continuous variables will be described by means and SDs, supplemented by minimum, median, percentiles and maximum. In addition, data will be analysed graphically (e.g., boxplot). Number of missing values will be reported for all variables of interest. Cases with missing values will be compared with those with complete data with regard to characteristics relevant for study outcomes.

The primary outcome is the improvement of empowerment 6 month after t_0_ (EPAS-t_2_) compared to baseline (EPAS-t_0_). Therefore, a hierarchical linear model (mixed model approach [30, 31]) is used to model EPAS-t_2_ as outcome and intervention, baseline EPAS-t_0_, centre and centre-size as main regressors with special attention to the intervention (confirmatory). The significance level will be set to 5% for intervention. The analysis will be based on a modified intention-to-treat (modITT)-population, using all patients with an outcome at month six (EPAS-t_2_) [32], since an imputation of the primary outcome can be misleading. Data management procedures will be implemented to reduce the drop-out rates; thus, a relatively low drop-out rate is expected. To examine a possible selection bias, the baseline data of ITT and modITT populations will be compared. In case of differences, these variables will be included in the regression models to adjust for confounding. For the independent variables, mixed model approaches can handle missing data well, and thus, no multiple imputation is needed in particular. However, according to this modITT concept, multiple imputation [33] of missing data in independent variables will be conducted by fully conditional specification (FCS) to perform a sensitivity analysis.

Other possible confounders with respect to the main outcome will be investigated by adding them into the model, eventually using backward selection procedures for variable selection and multiple imputations (*see* above). These analyses will be subjected to explorative interpretation only.

All other outcomes (*see* chapter ‘Outcomes and measurement’) will be analysed in a similar way. Subgroup analyses will be conducted separated by recruiting centres. Patient-related analyses (knowledge, attitudes, and experiences, service use, satisfaction with treatment, treatment needs and quality of life) will be conducted separately for patients with F2x and F3x diagnoses in additional subgroup analyses. Other categorisations based on quantitative variable are not planned.

Health economic evaluation (HEA) will be conducted from the societal and from the payer (statutory health insurance) perspective. Incremental cost-utility ratios (ICUR) will be computed using the differences in total (direct and indirect) costs of illness and the differences in quality-adjusted life years (QALY) between study groups over 12 months for the societal perspective. For the HEA from the payer perspective only the direct costs reimbursed by the statutory health insurance will be used as ICUR numerator. For both perspectives the stochastic uncertainty of the ICUR will be estimated by means of nonparametric bootstrapping with 2000 replications [34]. Probability of cost-effectiveness at MWTP for the gain of one QALY in the range between 0 and 100,000 € will be estimated for both perspectives by means of the cost-effectiveness acceptability curve [34]. The calculation of the QALY is based on the EQ-5D-5 L by means of the German value set [23].

All analyses will be conducted separately for patients and relatives.

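### The primary model lists centre as a regressor although each centre lies wholly in one arm; the intervention effect is estimable only with centre as the random level, which the text does not say

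*Protocol article*

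**What the plan says.** Under Randomisation, the article makes the centre the unit of allocation: "The 10 recruiting centres will be randomised 1:1 to the intervention and control group using the size of centre (small, large) as strata". All patients of a centre therefore share one arm and one size class.

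Under Statistical methods, the primary analysis is introduced with "Therefore, a hierarchical linear model (mixed model approach [30, 31]) is used" and continues "to model EPAS-t_2_ as outcome and intervention, baseline EPAS-t_0_, centre and centre-size as main regressors with special attention to the intervention (confirmatory"). The test level follows: "The significance level will be set to 5% for intervention". Centre appears in the same list as intervention, baseline score and centre size. None of the four is called fixed or random, and no random intercept is mentioned. The same section says the other outcomes will be handled similarly and plans subgroup analyses by recruiting centre.

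Under Sample size, the centre is treated as the source of correlation: "We assume a liberal intra-class correlation coefficient of 0.02 to control for the correlation of the outcome of participants of the same centre".

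**The concern.** This sentence defines the only confirmatory test. In a trial that randomises whole centres, arm and size class are both properties of the centre. A set of centre indicators therefore already contains all the information in the intervention and centre-size columns. Fitted that way, the model has no unique intervention coefficient. Software that drops redundant columns would still print one, but its value would depend on which centres serve as reference.

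The planned subgroup analyses by centre point to the same gap. Inside one centre all patients are in one arm, so there is no intervention contrast to estimate. Because the other outcomes are to be analysed in a similar way, the unclear role of centre carries over to them.

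A second matter arises once centre is made random. The intervention is then judged against variation between only 10 centres, so the reference distribution affects both the error rate and the power.

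**Working it through.** **Inputs** (Sample size and Randomisation sections): 10 centres, 5 per arm; m = 35 analysed per centre ("We assume that each centre recruits 35 patients (m) on average"), so 350 analysed; ICC 0.02; effect 0.4 SD; 5% level; 80% power. Sidedness is not stated; two-sided is assumed, as it reproduces the stated number. The count of large centres is not given, so it was varied.

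**1. The plan's own figures.** The normal approximation for 0.4 SD, two-sided 5% and 80% power gives 99 per arm. At the stated 100 per arm, t-test power is 80.4%. DE = 1 + 34 × 0.02 = 1.68; 200 × 1.68 = 336; 336/35 = 9.6, so 10 centres; 35/0.7 = 50 per centre, 500 in all. These reproduce.

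**2. Estimability.**

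| Role of centre | Columns | Rank | Intervention estimable |
|---|---|---|---|
| Fixed: intercept + intervention + baseline + size + 9 centre indicators | 13 | 11 | No |
| Random intercept; fixed part is intercept + intervention + baseline + size | 4 | 4 | Yes |

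The result is the same with 2, 4, 5 or 6 large centres. The deficiency of 2 arises because intervention and size are each sums of centre indicators. With a random intercept at ICC 0.02 and a true effect of 0.40, 2,000 simulated trials analysed by generalised least squares gave a mean estimate of 0.401, an empirical SD of 0.139 and a model SE of 0.139.

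**3. Type I error with centre random.** The article names no reference distribution, so these figures are conditional on the one chosen. Setting: 200,000 null trials per row, 35 per centre, REML with the centre variance truncated at zero, no baseline covariate; where size is in the model, 4 large centres split evenly between arms.

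| ICC | Size in model | Centre variance estimated as zero | Normal reference | t reference |
|---|---|---|---|---|
| 0.02 | no | 21% | 6.9% | 3.6% (8 df) |
| 0.02 | yes | 23% | 7.0% | 3.3% (7 df) |
| 0.05 | no | 5% | 8.2% | 4.7% (8 df) |
| 0.05 | yes | 7% | 8.4% | 4.4% (7 df) |

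The 7 df are 10 centres minus 3 centre-level parameters (intercept, intervention, size). ICC 0.05 is an assumption to show the range; the plan's value is 0.02.

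**4. Power and interval width.** SE = √(4 × 1.68/350) = 0.1386, and 0.4/0.1386 = 2.887.
- Normal reference: Φ(2.887 − 1.960) = 82%.
- t, 8 df (critical value 2.306, noncentral t): 72%.
- t, 7 df (critical value 2.365): 70%.
- Interval width, 7 df against normal: 2.365/1.960 = 1.21, so about 21% wider.

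This takes 0.4 SD on the unadjusted scale, as the plan does. Baseline adjustment would raise power, but the article gives no baseline correlation from which to say by how much.

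**The case against.** The strongest reply is that the sentence names a hierarchical, mixed model. Each patient contributes one 6-month score, with baseline as a covariate, so no repeated measures carry a random effect. Centre is the only grouping level described. The sample size calculation uses a centre-level ICC, and the Randomisation section calls the centres clusters. If centre were purely fixed, nothing in the model would be hierarchical. On that view the random intercept is what was meant, and listing centre size beside it is simply a level-2 covariate with its grouping unit.

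Most of this stands. A reader might infer that the confirmatory test, as planned, yields no valid estimate. The article does not support that: the named model class makes the random reading the more likely one, and under it the effect is estimable without bias. What remains is that the text gives centre the role of a regressor, in one list with the fixed covariates, and never says otherwise. The centre-wise subgroup analyses show that the nesting is not handled consistently.

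A reader might also infer that the 5% level is not held. That does not follow either. The article states no Wald test, estimation method or degrees of freedom, and such details are commonly left to an analysis plan. The 7% and 8 to 9% figures show what a normal reference would do; they do not describe a choice the plan has made. At the planned ICC the t reference errs the other way, at 3 to 4%.

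**Conclusion.** The point holds as a badly fixed specification of the confirmatory model. Followed literally, with centre as a fixed regressor, the model is rank deficient by 2 and has no estimable intervention effect; this depends only on whole-centre randomisation. With centre as a random intercept the effect is estimable, and that is probably what is intended, but the text does not say so.

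The consequences for error rate and power are conditional. They assume equal centres of 35 analysed patients, the stated ICC (0.05 shown for range), and a reference distribution that the article leaves open. The planned 80% comes from a t-test on individuals inflated by a design effect, which makes no allowance for having only 10 centres. On 7 to 8 df, the same assumptions give about 70 to 72%.

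**What to change.** Remove centre from the list of main regressors and state the model in one sentence: the 6-month EPAS score on intervention, baseline EPAS and centre size as fixed effects, with a random intercept for centre, fitted by REML. Keep the random intercept even if its variance is estimated as zero. Test the intervention with Kenward-Roger or with between-centre degrees of freedom (about 7). Carry the same structure over to the other outcomes, and describe the results by centre as descriptive, since they contain no arm comparison.

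The edit is short and changes no patient procedure or recruitment figure. It does have a statistical price: an interval about 21% wider than under a normal reference, and power of about 70 to 72% with 350 analysed. The Sample size section should restate the 80% on the chosen reference, giving any credit taken for baseline adjustment together with the correlation assumed for it.

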### Eligibility criteria

Inpatients and day hospital patients will be included if they have a severe mental disorder according to the definition of the S3 guideline ‘Psychosocial interventions in severe mental disorders’ (disease duration of ≥ 2 years and substantial impact on activities of daily life) [1]. However, in contrast to the S3 guideline, the inclusion criteria for the present study will be limited to patients with schizophrenia, schizotypal and delusional disorders (ICD-10 F2x) or mood [affective] disorders (ICD-10 F3x) to obtain a more homogenous sample [10]. Considerable consequences on the activities of daily life will be defined as a ‘Global Assessment of Functioning’ (GAF) [11] score ≤ 60 and a ‘Health of the Nation Outcome Scales’ (HoNOS) [12] fulfilling one of two conditions: (a) a score of ≥ 2 on one of the items of the subscale for symptomatic problems (items 6, 7 and 8) and a score of ≥ 2 on each of the four items of the subscale for social problems (items 9, 10, 11 and 12) or (b) a score of ≥ 3 on at least one of these items (9, 10, 11 or 12). Patients of all sexes will be included if they are between the ages of 18 and 65 years. Patients need to have sufficient capacity to understand the research project and to decide about their participation. In case of doubts about the ability to obtain consent of the patient, the responsible physician will decide on the capacity to consent. Legal representatives of patients (if available) will be informed about the study participation in case of consent from the patient.

To include the perspective of relatives of patients with mental disorders, relatives of all sexes will be included if they are aged over 18 years and if they are capable of understanding the research project. Relatives will only be included if they are not in current inpatient or day hospital mental health care.

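### The confirmatory EPAS-t2 model leaves out diagnosis group and setting, at a modest cost in precision; separately, the F2x/F3x analyses do not name the primary outcome

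*Protocol article*

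**What the plan says.** Under Eligibility criteria, the article admits inpatients and day hospital patients, "limited to patients with schizophrenia, schizotypal and delusional disorders (ICD-10 F2x) or mood [affective] disorders (ICD-10 F3x". Under Randomisation, ten centres are allocated 1:1, with centre size (small, large) as the only stratification factor.

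Under Statistical methods, EPAS-t2 is modelled with intervention, EPAS-t0, "centre and centre-size as main regressors with special attention to the intervention (confirmatory". Neither diagnosis nor setting is named. Two further routes to adjustment are described:

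- Baseline data of the ITT and modITT populations are compared, and variables that differ are added to the regression models.
- "Other possible confounders with respect to the main outcome will be investigated by adding them into the model", possibly with backward selection. These models are to be interpreted as exploratory only.

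On analyses by diagnosis the article says: "Patient-related analyses (knowledge, attitudes, and experiences, service use, satisfaction with treatment, treatment needs and quality of life) will be conducted separately" for F2x and F3x patients. The parenthesis is worded as a complete list, and empowerment is not in it.

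**The concern.** With five clinics per arm and balance sought on size alone, the arms can differ by chance in the share of F2x patients or of day hospital patients. If diagnosis or setting predicts EPAS-t2 beyond what EPAS-t0 already explains, that variation stays in the between-clinic and residual variance and widens the interval for the intervention effect. A patient-level covariate would remove it without using centre-level degrees of freedom, which are scarce here.

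Neither existing route closes the gap. The ITT-versus-modITT comparison sets all patients against those retained; if retention is similar but case mix differs between arms, it triggers nothing. The exploratory models cannot change the confirmatory result.

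A second, separate matter is that the plan looks at diagnosis for several secondary outcomes but not for the primary one. Consistency of the empowerment effect across the two enrolled groups is therefore not a planned analysis.

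**Working it through.** **Reproducing the plan's figures** (Sample size section). The inputs are, for the effect, "a medium effect (0.4 SD units) of the implementation intervention on the primary endpoint is expected"; for the test and its error rates, "error probability of 5% (alpha) and a power of 80% by a t-test for independent samples"; a size of 100 per arm before any allowance for clustering; for the cluster size, "We assume that each centre recruits 35 patients (m) on average"; ICC 0.02; 70% reached at six months.

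- Two-sided 5%, 80% power, 0.4 SD: 99 per arm by the normal formula; 100 per arm gives 80.4% by the t-test. The stated 2 × 100 reproduces.
- Design effect 1 + 34 × 0.02 = 1.68; 200 × 1.68 = 336; 35/0.7 = 50; 10 × 50 = 500. All reproduce.

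**Baseline for the comparison.** With 10 × 35 = 350 analysed, total variance 1 and ICC 0.02:

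- Var(arm difference) = (2/5) × (0.02 + 0.98/35) = 0.0192, so SE = 0.139.
- Power = Φ(0.4/0.1386 − 1.96) = 82.3%.

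**Effect of adding a binary case-mix covariate.** The documents give neither the spread between clinics nor the prognostic effect, so both are assumed:

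- *s* = between-clinic SD of the share, 0.05 to 0.20
- *g* = shift in EPAS-t2 given EPAS-t0, 0.1 to 0.3 SD
- overall split 50:50; two covariates taken as independent

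Adjustment removes g²s² between clinics and g²(0.25 − s²) within clinics.

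One covariate:

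| s | g | SE | Power |
|---|---|---|---|
| none | none | 0.139 | 82.3% |
| 0.05 | 0.1 | 0.138 | 82.4% |
| 0.10 | 0.2 | 0.138 | 82.8% |
| 0.20 | 0.3 | 0.132 | 85.5% |

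The gain is about 0 to 3 points, and the SE falls by at most about 4%.

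Two covariates:

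- s = 0.10 for both, g = 0.2: between 0.04 × 0.02 = 0.0008, within 0.04 × 0.48 = 0.0192. Var = 0.4 × (0.0192 + 0.9608/35) = 0.01866, SE 0.137, power about 83%.
- s = 0.15 and 0.20, g = 0.3: between 0.09 × 0.0625 = 0.0056 (28% of the ICC), within 0.09 × 0.4375 = 0.0394. Var = 0.4 × (0.0144 + 0.9406/35) = 0.0165, SE 0.128, power 87.6%. Counting only the between-clinic part gives 86.6%.
- Extreme corner, s = 0.20 for both, g = 0.3: Var = 0.4 × (0.0128 + 0.9422/35) = 0.01589, SE 0.126, power 88.8%.

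The first two scenarios gain about 1 and 5 points, the corner about 6.5. With the smallest effects (g = 0.1) the gain is under 1 point.

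**Chance imbalance.** The arm difference in a share has SD s × √(2/5): 6 percentage points at s = 0.10 and 13 at s = 0.20. In the 0.15/0.20 scenario the resulting shift has SD √(0.4 × 0.0056) = 0.047. It is already part of the planned SE: √(0.1386² − 0.047²) = 0.130, which is the SE once the between-clinic part is removed. It is the same quantity as the power gain, seen from another side.

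**The case against.** The strongest defence is that baseline outcome plus the stratification factor is a respectable pre-specified model, and that adding covariates is a preference about efficiency. EPAS-t0 absorbs most case-mix difference visible at admission, and no document figure shows that clinics differ in diagnosis or setting. This largely stands. It is why the gain is given as a range under assumptions, and why clinics *may* differ is as far as the text allows.

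Several stronger readings are tempting, and the documents do not support them:

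- *The omission biases the effect.* Chance imbalance in a randomised comparison is not bias. If centre is a random effect, as a hierarchical model suggests though the article does not say so, this variation is carried into the SE.
- *Recruitment makes the case mix differ between arms.* The Discussion foresees unequal recruitment numbers; it says nothing about an unequal mix of diagnoses.
- *Diagnosis can enter only through exploratory models.* The ITT-versus-modITT route sits in the paragraph on the confirmatory analysis. It is conditional and does not compare arms, but it exists.
- *Leaving EPAS off the F2x/F3x list puts noise into the primary effect.* A subgroup list has no bearing on the main effect. Nor does it bar anyone from adding the analysis later; such an analysis would simply be unplanned.
- *Both variables are already recorded.* Diagnosis is, as eligibility and as medical history. Setting is implied by eligibility but is not listed as a data item.

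**Conclusion.** The point holds as a modest, avoidable loss of precision, together with a separate gap in the planned diagnosis analyses. It does not make the primary analysis invalid and leaves the stated sample size untouched.

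The size rests wholly on assumed clinic spreads and on prognostic effects beyond EPAS-t0: about 0 to 3 points of power for one covariate and about 1 to 5 for two in moderate scenarios, from 82% to some 87 to 88% by the plan's own formula. It is near zero if EPAS-t0 captures most of what diagnosis and setting predict. The omission of empowerment from the F2x/F3x list needs no assumption, since it is on the page.

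The change is worth making even at the low end, because it costs almost nothing and removes a later, data-driven choice between adjusted and unadjusted results.

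**What to change.** In Statistical methods, name diagnosis group (F2x/F3x) as a patient-level covariate in the confirmatory EPAS-t2 model, beside EPAS-t0 and centre size. Do the same for setting at admission (inpatient/day hospital), provided it is recorded at t0; if it is not yet a data item, add it to the baseline form.

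In the F2x/F3x sentence, add EPAS-t2, reported as the difference in intervention effect between diagnosis groups (intervention-by-diagnosis interaction) with its 95% CI and labelled exploratory.

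The cost is a sentence for each change. The two covariates use 2 patient-level degrees of freedom out of about 350 observations and none at centre level. Diagnosis is needed for eligibility, so it should be complete.
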